### Randomization procedure

The recruitment started by listing all the schools in a Southern part of Finland. After choosing the schools (including as many classes of the same grade as possible), a letter explaining the study procedure was sent by e-mail to the head masters. Within few days after sending the information letter, the research team members called the headmasters by telephone. In most schools the decision to take part to the study was made collectively by the head master and the class teachers (of the chosen grades). The schools were enrolled from 14 cities/municipalities during the collection of the data (years 2014–2016). Altogether 247 schools were contacted, 59 of those participated in the study participation percentage being 24. In each municipality we aimed at an equal number of intervention and control classes. In order to achieve balanced intervention and control groups, schools participating in the study were randomized using the available background variables. The selection of intervention-control pairs was primarily based on the language being used for teaching (Finnish, Swedish or English, the grade, the school location, the number of classes participating in the investigation and, if necessary, the average apartment price per square meter in the school’s neighborhood).

The classes were randomly assigned to mindfulness intervention classes (*N* = 85) and control classes (*N* = 79) and non-treatment classes (*N* = 28). Due to practical reasons, in spring 2014 and in autumn 2015 schools were divided into two arms (intervention and control) and in spring 2015 and spring 2016 into three arms instead of two: intervention, control and non-treatment groups. First, the schools were divided into three groups based on the school location and the average apartment price per square meter. Within each of these groups, the total number of schools and classes varied. Next, the schools for these groups were divided into three subgroups including approximately same number of classes (some schools were combined into one subgroup to achieve an as even distribution of classes as possible).

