## Methods

### Trial design

The study is an ongoing cluster randomized controlled trial (RCT) with three arms. Eligible schools were randomly allocated either to an intervention, control or non-treatment groups. Clusters were school classes (grades 6, 7 and 8) and age gap was from 12 to 15 years olds. The data collection started in the spring 2014, and finishes in the autumn 2016. The analyzing and reporting of the data starts in the autumn 2016.

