## Sample size

The sample size was estimated to detect the mean difference of 0.2 standard deviation units (effect size = 0.2) on main outcomes of risk for depression (RBDI), social/emotional/behavioural skills (SDQ) and resilience (RS14) between intervention and control groups with 80 % power and the two-tailed 5 % level of significance. The clustering of outcomes within schools was taken into account, assuming an intra-cluster (intra-school) correlation coefficient of 0.03 and assumed that on average 60 children in each school will complete the study. The required sample size was estimated to be 1090 children per group, and allowing for about 10 % drop-out rate, the study requires 1200 children per group and total of 2400 children to be recruited. On the RBDI and SDQ total difficulties score, an effect size of 0.2 corresponds to a mean decrease of 0.8 score on the RBDI scale and a mean decrease of 1.0 score on the SDQ scale, assuming the standard deviations of 4 for RBDI [62] and 5 for SDQ [61]. The effect size of 0.2 corresponds to a mean increase around 2.5 score on the resilience scale, assuming the standard deviation of 13 [70].

In addition to comparing the intervention and control groups, we were interested in comparing the intervention and non-treatment groups in order to gain even more strength into the study design. However, this was not our primary intrest. Since the previous research has shown also standard relaxation programs to have beneficial effects on well-being, we are expecting to find greater differences between intervention and non-treatment groups compared to intervention and control groups. Using the same assumptions to detect the mean difference of 0.3 standard deviation units (effect size of 0.3) between intervention and non-treatment group, the required sample size was estimated to be 486 children per group, and allowing for about 10 % drop-out rate, the study requires 540 children in the non-treatment group.

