## Analysis plan

Data will be analyzed on an intention to treat basis including all randomized classes in the groups to which they were randomly assigned. Descriptive statistics (mean, median or percentages as appropriate) will be used to summarize the baseline characteristics and outcomes in each group.

Statistical analysis will be done with multilevel (hierarcial) models to account for the clustering within schools. Continuous outcomes will be analysed with linear mixed effects models and categorical outcomes with generalized linear mixed effects models. Maximum likelihood estimation will be used to get unbiased and efficient parameter estimates for data with missing values in the follow-up measurements.

The effectiveness of the mindfulness intervention on primary and secondary outcomes will be first analyzed using unadjusted analyses and then adjusted for age, sex and baseline values of the outcomes. The modifying effect of factors (i.e. sex, childen’s age, health status, circumstances at home, social relationships, hobbies, school achievement) on the effectiveness of mindfulness will be analysed using tests of interactions. Interaction analyses are exploratory in nature. The differences in the continuous outcomes between groups will be presented using mean differences with 95 % confidence intervals. Results are expressed using odd ratios with 95 % confidence intervals for categorical outcomes. Two-sided statistical tests with a 5 % level of significance will be used.

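### In the three-arm terms arms appear to have gone to subgroups of schools within location/price groups, but power and model account only for clustering within schools, so error bars for the non-treatment contrast can be wrong in either direction

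*Protocol article*

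**What the plan says.** The protocol article describes the unit of allocation in three ways.

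- **School.** Trial design: "Eligible schools were randomly allocated either to an intervention, control or non-treatment groups". The same paragraph then calls school classes the clusters.
- **Class.** Randomization procedure states that classes were randomly assigned: 85 to mindfulness, 79 to control and 28 to non-treatment.
- **Subgroup of schools.** Randomization procedure, on the two spring terms (2015 and 2016) that had a third arm, describes a first step of sorting schools into three groups by location and apartment price. As the second step, "the schools for these groups were divided into three subgroups including approximately same number of classes". A remark in brackets adds the detail that matters here, namely that "some schools were combined into one subgroup to achieve an as even distribution of classes as possible". The description stops there. It does not say how arms were given to subgroups, or how many schools were combined.

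The quantitative sections use one level only. Sample size: "The clustering of outcomes within schools was taken into account, assuming an intra-cluster (intra-school) correlation coefficient of 0.03", with 60 completers per school. Analysis plan: "multilevel (hierarcial) models to account for the clustering within schools". Neither section mentions the subgroup or the location/price group. The adjusted model lists age, sex and baseline value of the outcome.

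**The concern.** With three arms and three subgroups in each location/price group, one arm per subgroup is the obvious purpose of the scheme. Combining schools to even out class counts serves balance only if the combined schools share an arm. On that reading the allocated unit in these terms is a subgroup of one or more schools, inside a stratum that all three arms share.

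A school-only analysis then leaves out two features of the design, which act in opposite directions. If schools in one subgroup resemble each other more than they resemble schools in the other subgroups of the same stratum, standard errors are too small. If the shared variation lies between location/price groups, every arm carries it equally, and leaving the stratum out makes standard errors too large.

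What is at stake is mainly the interval and p-value for mindfulness versus non-treatment, whose concurrent data come entirely from these terms and may rest on about six allocated units per arm.

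**Working it through.** **Inputs from the article.** ICC 0.03, 60 completers per school, 80% power, two-sided 5%, effects 0.2 and 0.3 SD, stated n of 1090 and 486 (Sample size). Mindfulness plus Relax students by term: 523, 1090, 821, 203; non-treatment: 254, 109 (Data collection timeline). 59 schools; 85, 79 and 28 classes (Randomization procedure).

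**1. The plan's own figures.** Design effect (DE) = 1 + 59 × 0.03 = 2.77.
- 0.2 SD: 393 × 2.77 = 1088.6 (t-based 394 × 2.77 = 1091.4); stated 1090.
- 0.3 SD: 175 × 2.77 = 484.8 (t-based 176 × 2.77 = 487.5); stated 486.

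Both reproduce with the school as an independent cluster, so no other level entered the calculation.

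**2. Data from the three-arm terms.**
- Non-treatment: 254 + 109 = 363, which is all of it.
- Mindfulness and Relax: (821 + 203)/(523 + 1090 + 821 + 203) = 1024/2637 = 39%. The other 1613 (61%) come from two-arm terms.

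**3. Number of units.** 192/59 = 3.25 classes per school, so 28 non-treatment classes are about 8.6 schools. If the scheme ran in each term (assumption), there are 3 × 2 = 6 subgroups per arm, or about 8.6/6 = 1.4 schools each.

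**4. Subgroup similarity alone (the direction that makes standard errors too small).** DE = 1 + 59 × 0.03 + 60 × (m − 1) × ρ. Here m is schools per subgroup and ρ is the extra correlation between schools of one subgroup. The article gives neither, so both are assumptions. The SE ratio is √(DE/2.77).

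| m | ρ | DE | n per group, 0.3 SD | SE ratio |
|---|---|---|---|---|
| any | 0 | 2.77 | 485 | 1.00 |
| 1.5 | 0.005 | 2.92 | 511 | 1.03 |
| 1.5 | 0.01 | 3.07 | 537 | 1.05 |
| 2 | 0.005 | 3.07 | 537 | 1.05 |
| 2 | 0.01 | 3.37 | 590 | 1.10 |
| 2 | 0.03 (whole ICC) | 4.57 | 800 | 1.28 |

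For mindfulness versus Relax, apply the excess to 39% of the data: DE = 2.77 + 0.388 × (DE from the table − 2.77). With m = 2 and ρ of 0.005 or 0.01, the SE ratio is 1.02 or 1.04, and power at 1090 per group is about 0.785 or 0.77.

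**5. Both directions, non-treatment contrast.** Simulated null trials: 6 strata, one subgroup per arm in each, 1 or 2 schools per subgroup, total ICC 0.03, about 51 students per school (3000/59). The test is a school-level t-test that ignores stratum and subgroup. Each row has 20,000 trials, so the Monte Carlo SE near 5% is about 0.15 points.

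| Stratum variance | Subgroup variance | Rejection at nominal 5% |
|---|---|---|
| 0 | 0 | 4.9% |
| 0 | 0.01 | 6.9% |
| 0 | 0.02 | 8.0% |
| 0.01 | 0 | 3.5% |
| 0.02 | 0 | 2.2% |
| 0.01 | 0.01 | 4.8% |

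With subgroup variance 0.005 and no stratum variance, the rate was about 5.8%. A test on subgroup means within stratum stayed at about 4.6% to 5.3%. A fresh run of the same set-up gave the same pattern in both directions.

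**The case against.** The strongest reply has four parts.

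- **The premise is inferred.** The article never writes that a subgroup received an arm, and says only that some schools were combined. This stands. What is firmly documented is an inconsistent description of the allocated unit.
- **The direction is unknown.** A reader might infer that the trial's standard errors are too small. The documents do not support that. Schools were combined to even out class counts, which gives no reason to expect them to be alike. Similarity in location and price belongs to the stratum, and ignoring it widens intervals. With 0.01 at each level the two nearly cancel. This stands too, but it is no defence of the school-only model: once the stratum is fitted the offset goes, and any subgroup component remains.
- **The main comparison is barely touched.** This stands. The Sample size section also says the non-treatment comparison was not the primary interest. Adjustment for baseline would be expected to remove part of any shared variation, which the simulation ignores.
- **The random-effect structure may be in an SAP that is not shown.** This stands in part. The article does not say that school is the only random effect. But it does fix the clustering level for power and model, and it contradicts itself on what was allocated. Those statements need reconciling whatever the SAP holds.

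**Conclusion.** The point holds in a limited form. The article implies, without stating it, that in spring 2015 and spring 2016 arms went to subgroups of one or more schools within three location/price groups. Power and model recognise only the school, and the school and the class are also named as the allocated unit.

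For mindfulness versus non-treatment, the true size of a nominal 5% school-only test could plausibly lie between about 2% and 8%. This assumes six subgroups per arm, one or two schools each, a total ICC of 0.03, and up to 0.02 of it at stratum or subgroup level. It would be close to 5% if neither component exists or if they offset. For mindfulness versus Relax the effect is small: SE understated by about 2% to 4%, if at all, for a subgroup correlation of 0.005 to 0.01 with two schools in every subgroup. Nothing here shows that the stated sample sizes are miscalculated; they are right for the clustering they assume.

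**What to change.** 1. State the allocation unit and the number of units per arm for each term, including how arms were assigned to subgroups and how many schools were combined. Reconcile the statements naming class, school and subgroup.
2. For the three-arm terms, include the location/price group (by term) in the model.
3. For mindfulness versus non-treatment, report alongside the mixed model a subgroup-level analysis: a paired test, or a permutation test that re-assigns arms to subgroups within each location/price group.
4. Do not rely on a subgroup random effect alone. In simulated data with about 27 schools in 18 subgroups, REML set that variance to zero in 37%, 35% and 23% of fits when the true value was 0.005, 0.01 and 0.02. The model then falls back to school only.

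**Cost.** The identifiers should already exist in the allocation records. The statistical price is real: with about six units per arm, the subgroup-level interval is roughly 15% to 25% wider than a stratum-adjusted school-level one when the subgroup component is 0.01 or less. Much of that is degrees of freedom. A paired test on six strata has 5 df (t = 2.57). About 18 schools less 7 parameters leaves 11 df (t = 2.20), and 2.57/2.20 = 1.17. The permutation test has 2^6 = 64 swaps, so the smallest two-sided p is 2/64 = 0.031 and the next is 0.0625. At 5% it is therefore somewhat conservative.

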### Data collection timeline

The data from intervention and control groups have been collected during four academic terms: In the beginning of spring term in 2014 (*N* = 523), in the beginning of autumn term in 2014 (*N* = 1090), in the beginning of spring term in 2015 (*N* = 821), and in the beginning of spring term in 2016 (on going, baseline including *N* = 203). Hence the last follow-up will be collected in spring 2017 (12 months follow-up of the spring 2016). Among intervention and control groups data have been collected at baseline, in the middle of the intervention (the fifth week of the intervention, a short formula), within 1 week after the intervention, and 6 and 12 months after baseline from the same participants.

Due to practical reasons, the data from non-treatment group have been collected during two academic terms: In the beginning of spring term in 2015 (*N* = 254), and in the beginning of spring term 2016 (ongoing, baseline including *N* = 109). Additionally, non-treatment group did not fill in the short formula in the middle of the intervention the measurement points being otherwise identical with the other two groups (incl. follow-ups).

Among teachers and parents data have been collected at baseline, after the intervention and 6 months after the baseline from the same parent (if only one parent filled-in the formula) and from the same teacher. In a case the teacher had left/changed between the different measurement points, only the grades and absence from school of students were asked (from the new teacher).

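### The intervention versus non-treatment contrast has no term effect and no restriction to the two terms in which non-treatment could be allocated, so recruitment term is partly confounded with arm

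*Protocol article*

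**What the plan says.** Protocol article, Randomization procedure: "in spring 2014 and in autumn 2015 schools were divided into two arms", namely intervention and control (Relax), whereas schools were divided "in spring 2015 and spring 2016 into three arms instead of two: intervention, control and non-treatment groups".

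Protocol article, Data collection timeline: "The data from intervention and control groups have been collected during four academic terms", with 523, 1090, 821 and 203 students. For the third arm: "Due to practical reasons, the data from non-treatment group have been collected during two academic terms", with 254 students in spring 2015 and 109 in spring 2016. The spring 2016 counts are marked as ongoing. This section dates the autumn cohort to 2014, not 2015.

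Protocol article, Sample size: intervention versus non-treatment is a planned comparison, powered for 0.3 SD and described as not the primary interest.

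Protocol article, Analysis plan: "Data will be analyzed on an intention to treat basis including all randomized classes", in the groups to which they were assigned. The models account for clustering within schools. They are run first unadjusted and then with age, sex and the baseline outcome as covariates. Recruitment term, cohort and randomisation stratum are not mentioned, and no analysis is limited to the three-arm terms.

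**The concern.** In spring 2014 and in the autumn term, no school could be allocated to non-treatment. Intervention classes from those terms are therefore non-concurrent comparators for the non-treatment classes. If they are pooled without a term effect, any difference between recruitment terms enters the estimated effect of mindfulness against no treatment.

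Season is a plausible source of such a difference. The largest two-arm cohort (1090) started in autumn, while every non-treatment student started in spring. The post-intervention and 6-month measurements therefore fall at different points of the school year in the two cohorts. A seasonal difference in change from baseline would line up with arm, and adjusting for the baseline level cannot take it out. The contrast would nevertheless be reported as a randomised effect.

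**Working it through.** **1. The plan's own figure.** Inputs from Sample size: effect 0.3 SD, 80% power, two-sided 5%, ICC 0.03, 60 children per school.
- Design effect: 1 + (60 − 1) × 0.03 = 2.77.
- Individually randomised size: 175 per group. 175 × 2.77 = 485, against 486 stated.
- Drop-out: 486 / 0.9 = 540, as stated.

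The planned size reproduces. It assumes one randomised comparison and does not consider terms.

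**2. Who was concurrent.** Inputs from Data collection timeline.
- Active arms: 523 + 1090 + 821 + 203 = 2637.
- Entered in two-arm terms: 523 + 1090 = 1613, and 1613 / 2637 = 61%.
- Entered in three-arm terms: 821 + 203 = 1024, or 39%.
- Autumn starters: 1090 / 2637 = 41%.
- Non-treatment: 254 + 109 = 363, all in three-arm terms.

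**3. The same share in the intervention arm alone.** Students by arm and term are not given. Let the intervention share of the active arms be a in two-arm terms and b in three-arm terms. The non-concurrent share is 1613a / (1613a + 1024b).
- a = b: 61%.
- a = 0.4, b = 0.6: 645.2 / (645.2 + 614.4) = 51%.
- a = 0.6, b = 0.4: 967.8 / (967.8 + 409.6) = 70%.

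**4. Bias in the unadjusted pooled contrast.** Assume equal splits and weighting roughly by student numbers. The bias is then the non-concurrent share times the outcome difference between the terms. The document gives no such difference, so 0.1 to 0.3 SD is an assumption.

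| Source of the difference | Factor | Bias at 0.1 SD | Bias at 0.3 SD |
|---|---|---|---|
| Two-arm versus three-arm terms | 0.61 | 0.06 SD | 0.18 SD |
| Autumn versus spring only | 0.41 | 0.04 SD | 0.12 SD |

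The second row is smaller because spring 2014 shares its season with both non-treatment terms.

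**5. Precision with and without the non-concurrent students.** SE = sqrt(2.77 × (1/n1 + 1/n2)). Power at 0.3 SD is Φ(0.3/SE − 1.96). A 1:1 intervention to Relax split is assumed: 2637 / 2 = about 1318 pooled and 1024 / 2 = 512 concurrent.
- Pooled, 10% drop-out: sqrt(2.77 × (1/1186 + 1/327)) = 0.104; power 82% (86% without drop-out).
- Concurrent, 10% drop-out: sqrt(2.77 × (1/461 + 1/327)) = 0.120; power 70% (75% without drop-out).
- Concurrent and stratified by term: SE 0.121 and power 70% with drop-out (74% without).

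**The case against.** Pooling over all terms is not stated for this contrast by name. It is inferred from an intention-to-treat sentence whose main purpose is to say that classes are analysed as allocated. A condensed article may also leave contrast-specific populations to an analysis plan that is not shown. This softens the point but does not remove it: the article itself names both the analysis set and the covariates, and term is in neither.

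A reader might infer that most of this contrast is not randomised. The documents do not support that. All 363 non-treatment students have intervention and Relax comparators randomised in the same terms, so confounding of arm with term is partial. The 61% describes the two active arms together, and applying it to the intervention arm needs an assumption about splits.

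Baseline adjustment deserves credit. It removes part of any stable cohort difference, so the adjusted analysis should be less biased than the table above. What remains is differential change by term.

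Nothing in the document shows that term differences reach 0.1 to 0.3 SD. The article argues that school-related variance in Finland is low, although it does not discuss season.

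The autumn 2014 versus autumn 2015 mismatch adds no weight to the confounding argument, because two of the four terms are two-arm terms on either date.

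**Conclusion.** The point holds for a secondary contrast and is of moderate weight. As written, the analysis of intervention versus non-treatment mixes concurrent and non-concurrent intervention classes and has no term effect. The possible unadjusted bias is about 0.04 to 0.18 SD against the 0.3 SD target. That range rests on assumed term or season differences of 0.1 to 0.3 SD and on equal intervention to Relax splits in each term. It is smaller after baseline adjustment, but not zero if change from baseline differs by term.

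A reader might also infer that the trial's main conclusion is at risk. It is not, on this ground: intervention and Relax were randomised side by side in all four terms, and the article declares the non-treatment comparison not to be its primary interest.

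**What to change.** 1. Include recruitment term as a fixed effect in every model that contains the non-treatment arm. Non-treatment is then compared with the other arms within spring 2015 and spring 2016, and every randomised class stays in the analysis.
2. Report the intervention versus non-treatment estimate restricted to those two terms, with term as a fixed effect. Either this or the term-adjusted four-term model can be the main analysis, with the other in support. The choice should be fixed in advance.
3. State the power honestly: about 70% to 75% at 0.3 SD from concurrent students, under a 1:1 split and the baseline counts reported so far, instead of the nominal pooled 82% to 86%.
4. Reconcile the date of the two-arm autumn term between Randomization procedure (2015) and Data collection timeline (2014), so that the concurrent terms are unambiguous.

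No new data are needed. The term effect costs only wording and few degrees of freedom. Under restriction the standard error rises from about 0.104 to 0.120 SD after drop-out. The precision given up comes from students who were never randomised against non-treatment.
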